### Consent

The investigator will provide complete verbal and written information to the patient and parents, checking the inclusion and non-inclusion criteria. Once eligible adolescents and their parents who have given their verbal consent, they will be referred to the study psychologist who will obtain the written consent of the parents and the adolescent. Subjects will be able to withdraw their consent and request to be removed from the study at any time for any reason. The investigator may temporarily or permanently discontinue a subject’s participation in the study for any reason that would be in the best interests of the subject, particularly in the case of serious adverse events. If a subject is lost to follow-up, the investigator will make every effort to re-establish contact with the person. In the case of a withdrawal of consent, the data collected will not be used in accordance with the patient’s wishes.

During their participation, patients will not be able to participate in research on addictive behaviours, and there are no restrictions on treatment.

An assessment of personality characteristics that represent a risk for the development of problematic substance use using the SURPS questionnaire will be carried out. Only adolescents with risk-related personality traits, according to at least one of the dimensions: negative thinking, sensitivity to anxiety, impulsivity and sensation-seeking on the SURPS, will be randomized. The others will be excluded from the randomized trial. Adolescents excluded prior to randomization will have a meeting with a psychologist to discuss the risks associated with addictive disorders and they will be given information about risk prevention.

### Intervention

The *Preventure* program consists of two 90-min sessions with delivered to small groups of students (i.e., approximately 4–6 students per group), led by a trained facilitator. In 2020, this program was adapted for online delivery via videoconferencing platforms and can now be accessed by adolescents on smartphones, tablets or computers. This online program enables wider access to the intervention for adolescents, whether they live in rural, semi-urban or urban areas .

Supported by real-life scenarios, and based on CBT and MI techniques, the sessions will incorporate:

1) Psychoeducation about the targeted personality trait (i.e., impulsivity, sensation seeking, anxiety sensitivity, hopelessness/negative thinking) and associated maladaptive coping behaviours.

2) The development of an individualized model of the physiological, cognitive and behavioural components of typical responses.

3) Motivational enhancement, goal setting and application of cognitive-behavioural skills to tackle problematic reactions and behaviour.

Each adolescent will receive the intervention corresponding to their predominant personality trait.

### Study design

This is a prospective, randomized, controlled, stratified, multicentre, open-label study aiming to evaluate the superiority of the *Preventure* program on the reduction of binge drinking episodes, over usual routine follow-up care forming the control group (individual follow-up consultations in primary care/or in adolescent care facilities/ adolescent addictive disorder consultations). It concerns a population of adolescents aged 14–17 having experimented with alcohol consumption.

The study design is presented in Fig. 1.

**Fig. 1 Fig1:**
[figure not shown]
Study design

### Randomisation

Adolescents will be randomised [1], and the randomisation will be stratified according to the predominant type of risk-prone personality trait (4 types) presented by the adolescents and according to recruitment conditions (school care vs. primary or specialised adolescent care). The control group will receive the usual routine follow-up (individual consultations in primary care / or in adolescent care facilities/ adolescent addictive disorder consultations) and assessments.; The intervention group will receive the usual follow-up, assessments plus the Preventure program tailored to one personality type among the 4 risk-related personality traits.

### Follow-up assessments

Adolescents will then be followed up and evaluated at 1, 3, 6 and 12 months after the intervention by a psychologist. Assessments will be offered to adolescents either by phone or during an interview lasting approximately 1 h, depending on their preference.

### SURPS: substance use risk profile scale

The Substance Use Risk Profile Scale (SURPS) is a screening instrument for personality traits identified as related to the risk of developing of addictive disorders. The SURPS consists of 23 items assessing four dimensions: Impulsivity, sensation-seeking, negative thinking and anxiety. The SURPS was created by Woicik et al. [17] and includes 23 items, to which young people are asked to respond using a 4-point Likert scale, ranging from strongly agree to strongly disagree: negative thinking (7 items), sensitivity to anxiety (5 items), impulsivity (5 items) and sensation-seeking (6 items).

The four different personality dimensions measured are associated with a high risk of developing addictive disorders. It was validated in French on a population of students from Quebec. The psychometric properties of the French version were satisfactory and comparable to previous studies and to the original version. The thresholds defined as risk-related were calculated according to means and standard deviations, and for the French version are: Negative thoughts = 15; Anxiety = 13; Impulsivity = 14; Sensation seeking = 17 [8].

### **Alcohol- timeline follow-back (TLFB)** [18]

The Alcohol-TLFB is a method of assessing alcohol consumption that provides an estimate of the daily amount of alcohol consumed in standard units (equivalent to 10 g. alcohol per drink). It has been evaluated among clinical and non-clinical populations and among adults and adolescents. It is presented in the form of a calendar.

Respondents report their daily consumption of alcohol over a specified period of the last 30 days. Reminders can be used when filling in the form (dates, events, etc.). This tool has good psychometric qualities and is recommended when precise information on the quantities of alcohol consumed or the number of days of consumption is required. It enables the number of days of alcohol consumption in the month and the number of days with alcohol consumption in excess of 5 standard units per day to be identified.

### **ADOSPA** [19]

The ADOSPA test is a French adaptation of the CRAFFT. It is a simple test for early detection of risky and harmful alcohol or drug use among young people. It consists of 6 questions. A score above 3 indicates high risk.

### **PedsQL4: Paediatric quality of life inventory version 4.0** [20]

The PedsQL 4.0 is a tool evaluating the quality of life of children, adolescents, or young adults (2 to 25 years old) in good health or with health problems. The 23 questions cover 4 different functioning areas: physical (8 items), emotional (5 items), social (5 items) and academic (5 items).

It is a questionnaire that can be self-administered, with the addition of a questionnaire dedicated to family and friends. The questionnaire intended for parents and relatives enables the parents to give an account of their perceptions regarding the quality of life related to their child’s state of health. It takes the child’s perceptions and those of his parents or relatives into account.

### **DSM 5: diagnostic and statistical manual of mental disorder** [21]

The diagnosis of substance use disorder is based on well-defined criteria set out in the Diagnostic and Statistical manual of Mental disorders (DSM), the fifth edition of which dates from 2013. The severity of SUD is classified as: mild (2 to 3 criteria) / moderate (4 to 5 criteria)/ severe (6 or more criteria).

### **AUDIT: alcohol use disorders identification test** Error! Bookmark not defined.

This is a simple 10-question test developed by the World Health Organisation to determine whether a person is at risk for alcohol addiction. A score between 7 and 12 for men and between 6 and 12 for women indicates risky or problematic drinking. A score above 12 indicates probable alcohol use disorder.

### **HONC: hooked on nicotine checklist** [22]

Di Franza’s Honc checklist (Hooked on Nicotine Checklist) is a 10-item test that highlights the loss of control over tobacco consumption. This tool is particularly suitable for young smokers. The scoring ranges from 1 to 10 with yes-no answers. A positive response to a single item is sufficient to indicate a loss of autonomy towards tobacco consumption. The higher the total number of positive responses, the more the test result suggests a loss of autonomy and therefore dependence. A score of 7 and above indicates a high level of dependence.

### **CAST: Cannabis abuse screening test** [23]

The CAST is a 6-item scale for identifying problematic cannabis use. Each of the items describes behaviours or problems encountered in the context of cannabis use. A score of 2 and above means a high risk of cannabis use disorder.

### **ADRS: adolescent depression rating scale** [24]

The ADRS test assesses depression among adolescents in 10 items. The items measure insomnia, anxiety, sadness and fatigability. The ADRS score enables the identification of a low risk of depression with a threshold > 4, moderate risk for a value between 4 and 8 or significant risk for a score > 8.

### Judgment criteria

The main criterion is the occurrence of at least one binge drinking episode (at least 5 Standard (US) Units of alcohol, equivalent to 50 g of pure alcohol/unit at one time) in the last month (evaluated at 6 months after intervention) measured with the Alcohol -Timeline Followback A-TLFB) proposed by (Sobell et al. 1998).

The secondary criteria are:

- Criteria for evaluating alcohol, tobacco or cannabis consumption: experimentation / use within the month / regular (more than 10 times a month), measured with the A-TLFB.

- Evaluation of alcohol, tobacco or cannabis consumption profiles: AUDIT, HONC, CAST and ADOSPA tests - Assessment of anxiety and depression: ADRS.

- Alcohol-related harm: collection of negative events linked to alcohol consumption in the past month, by interview.

- DSM-5 criteria for substance use disorders: alcohol / cannabis.

- Quality-of-life assessment: PedsQL V4.

- Assessment of the acceptability by adolescents: participation and retention rates in the study.

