### Inclusion criteria

Adolescents aged 14 to 17 years, seeking treatment in one of the participating centres in primary care, or adolescent care facilities (general or addictive disorder consultations for adolescents) or identified by a school doctor or nurse, who have already experienced alcohol (at least 1 standard unit of alcohol lifetime), will be included in the study, after written and informed consent from the parents and the adolescents. They are required to have Internet access, access to a smartphone, tablet or computer.

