### Non-inclusion criteria

The non-inclusion criteria will be the following: adolescents expressing refusal to participate in the study, or presenting moderate-to-severe substance use disorders (other than tobacco) or current non-stabilized psychiatric disorders, or current treatment for severe substance use disorders and/or severe psychiatric disorders (psychotic disorders, autistic disorders), or inadequate understanding of the French language. A lack of internet access, access to a smartphone, tablet or computer will also be a non-inclusion criterion.

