### Statistical analysis

The prevalence rates of adolescents who have experienced at least one binge drinking episode (more than 5 standard units) in the last month (measured at 6 months after intervention -main criterion) will be compared using logistic regression with adjustment for stratification factors between the two groups (intervention and control). As an exploratory measure, the interaction between the intervention and the type of risk profile will be tested, looking for possible heterogeneity of effect of the intervention according to the type of profile. In the case of a significant interaction, results by type of profile can be provided on an exploratory basis.

The binary secondary judgement criteria (pass/fail) will be analysed in the same way as the main criterion.

Quantitative judgement criteria will be analysed using a linear model with adjustment for stratification factors. The interaction term between intervention and profile type can be tested in the same way as for the main criterion.

Quantitative measurements repeated during monitoring will be modelled using a mixed linear model to take intra-subject correlation into account.

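### Experimentation is a secondary criterion for alcohol although prior alcohol use is an entry condition, and for tobacco and cannabis it is not limited to baseline never-users

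*Protocol article*

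**What the plan says.** Under *Judgment criteria*, the first secondary criterion covers alcohol, tobacco or cannabis consumption and is given as "experimentation / use within the month / regular (more than 10 times a month"), with the A-TLFB named as the measure. The text does not say whether the three terms are separate yes/no outcomes or levels of one scale. It does not limit the first term to adolescents who had never used the substance.

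Under *Inclusion criteria*, participants are those "who have already experienced alcohol (at least 1 standard unit of alcohol lifetime". *Study design* describes the same population as "having experimented with alcohol consumption".

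For tobacco and cannabis there is no ever-use or never-use condition. *Non-inclusion criteria* bars only adolescents "presenting moderate-to-severe substance use disorders (other than tobacco"), along with psychiatric, treatment and practical grounds.

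Under *Statistical analysis*: "The binary secondary judgement criteria (pass/fail) will be analysed in the same way as the main criterion". That analysis is a logistic regression adjusted for the stratification factors.

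The section on the Alcohol Timeline Follow-Back (A-TLFB) describes a calendar of daily alcohol consumption over the last 30 days.

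**The concern.** An outcome that the entry rule fixes for every participant cannot differ between arms. *Study design* applies the word experimentation to the entry population itself, and *Background* uses it for lifetime status in its statistic on French 14-year-olds. The ever/never reading is therefore a natural one, and on it the alcohol part of the criterion carries no information.

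For tobacco and cannabis the criterion can vary, but ever-use cannot revert. Anyone who tried the substance before randomisation is a yes in either arm. A prevention programme can only influence those who have not yet started, so the all-participant comparison mixes first use that the programme could prevent with first use that happened before it. An effect on initiation could then be reported as no effect on experimentation. Tobacco and cannabis use is among the secondary objectives in *Aim of the study*.

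**Working it through.** **1. The plan's own figure.** The only computed figure is the primary sample size: 50% versus 35%, alpha 0.05, power 80%, 170 per group. With a two-sided test and pooled variance under the null:

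n = [1.96·√(2·0.425·0.575) + 0.8416·√(0.50·0.50 + 0.35·0.65)]² / 0.15² = (1.370 + 0.582)² / 0.0225 ≈ 169.3, rounded up to 170.

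This reproduces the stated figure, and power at 170 per group is 80.2%. The point below does not touch this calculation. The same normal approximation is used in step 4.

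**2. Alcohol.**

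- *Ever/never reading.* The entry rule makes the proportion 100% in each arm at every visit. The difference is 0, the variance is 1·(1 − 1) = 0, and no odds ratio can be estimated.
- *Ordered reading* (experimentation only, past-month use, regular use). Everyone has used alcohol at some time, so the lowest level means only that there was no use in the month. That is the complement of the past-month criterion and adds nothing to it.

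**3. Tobacco and cannabis, ordered reading.** Prior use is not required, so lifetime never-users can enter. None of the three listed levels describes them.

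**4. Tobacco and cannabis, ever/never reading.** Let b be the share who had used the substance at baseline, and i the proportion of never-users who start during follow-up.

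- Ever-use at follow-up = b + (1 − b)·i
- Difference between arms = (1 − b)·(i_control − i_intervention)

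The article gives neither b nor i. The table assumes i = 30% (control) and 15% (intervention), b equal in the two arms, and 170 per arm all evaluated. The never-user analysis has 170·(1 − b) per arm.

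| b | Ever-use, control vs intervention | Difference (points) | Power, all 170 per arm | Never-users per arm | Power, never-users |
|---|---|---|---|---|---|
| 10% | 37.0% vs 23.5% | 13.5 | 78% | 153 | 88% |
| 30% | 51.0% vs 40.5% | 10.5 | 49% | 119 | 80% |
| 50% | 65.0% vs 57.5% | 7.5 | 29% | 85 | 65% |
| 70% | 79.0% vs 74.5% | 4.5 | 16% | 51 | 44% |

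Worked row, b = 50%, all participants: standard error under the null √(2·0.6125·0.3875/170) = 0.0528; under the alternative √((0.65·0.35 + 0.575·0.425)/170) = 0.0527; power = Φ[(0.075 − 1.96·0.0528)/0.0527] = Φ(−0.54) ≈ 29%.

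**5. Sensitivity to the assumed initiation rates.** At b = 10%, 30%, 50% and 70%:

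- 20% vs 10%: power 50%, 26%, 15%, 9% in all participants; 69%, 58%, 45%, 29% in never-users.
- 50% vs 35%: power 70%, 51%, 33%, 19% in all participants; 76%, 65%, 51%, 33% in never-users.

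The never-user analysis has the higher power in every case, despite the smaller number.

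**6. Instrument.** The criterion is said to be measured with the A-TLFB. As described, that tool covers alcohol only, over 30 days. It cannot show whether tobacco or cannabis has ever been used.

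**The case against.** The strongest reply is that the slashes suggest one ordered scale, and that the article calls experimentation neither lifetime nor binary. On that reading alcohol is not constant: adolescents can differ and can move between levels. The 30-day instrument named in the same sentence also sits awkwardly with a lifetime outcome. This stands to the extent that the statement about an unfittable model must be tied to the ever/never reading. It does not rescue the criterion, because the lowest alcohol level then repeats the past-month criterion and tobacco or cannabis never-users have no place. An article may leave out an obvious reference category, but here the published levels give the first term no useful meaning for alcohol on either reading.

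A reader might infer that many participants will already have tried tobacco or cannabis, so that dilution is heavy. The article does not support this. Addictive disorder consultations are one of several recruitment routes, and mild substance use disorder is not barred, so prior use is plausible. No rate is given, however, and at 10% baseline use the loss is mild. The initiation rates are likewise assumed, and the article claims no power for secondary criteria.

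A reader might also infer that lifetime use is not asked at baseline. The article does not itemise the baseline assessment and its design figure is not shown, so this cannot be concluded.

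Finally, detailed outcome coding often belongs in the analysis plan. That is fair for the coding, but here the published outcome and the published entry rule are themselves at odds.

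**Conclusion.** The point holds in conditional form. As an ever/never outcome, alcohol experimentation is 100% in both arms by design and cannot be analysed; as the lowest ordered level it is redundant. This follows from the article alone.

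For tobacco and cannabis, the shrinkage of an initiation effect by the factor (1 − b) is certain in direction on the ever/never reading. Its size depends on a baseline share that the article does not give. With the assumed 30% versus 15%, the all-participant comparison loses about 10 points of power at b = 10% and about 36 points at b = 50% (65% − 29%), relative to baseline never-users. These figures ignore attrition and covariate adjustment.

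One secondary criterion is affected. Past-month and regular use remain informative, and the primary endpoint and the 340 sample size do not change. This is a minor correction.

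**What to change.** - **Alcohol:** remove experimentation as an outcome.
- **Tobacco and cannabis:** define it as first use after randomisation among adolescents who reported at baseline that they had never used that substance. Analyse it with the same stratification-adjusted logistic regression.
- **Data:** take baseline status from lifetime use recorded before randomisation, adding one question per substance if it is not already asked. Name a source other than the A-TLFB as described, since that tool cannot supply this outcome.
- **Other levels:** keep use within the month and use more than 10 times a month as separate binary criteria in all randomised adolescents.

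The cost is a change of wording and at most one baseline question per substance. The never-user subset is fixed before randomisation, so the comparison remains randomised. The downside is a smaller analysis set. At b = 70% and the assumed rates there would be about 51·0.30 + 51·0.15 ≈ 23 events in total, so the initiation result could be imprecise and should be reported with its confidence interval.

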The main hypotheses of this study are that 1. the *Preventure* program will potentially have an impact on 1/ the prevalence of binge drinking episodes 2/ the number of days of alcohol consumption, 3/ associated substance uses: tobacco/ cannabis, 4/ anxiety and depression, 5/ alcohol-related harm, and 6/ quality of life. Moreover, it is also hypothesized that the Preventure program will be considered as an acceptable intervention among French adolescents.

This project could promote the targeted prevention of addictive behaviours among vulnerable adolescents. Thus, the use of the Preventure program could be considered on a larger scale and developed in primary care and schools or adolescent care facilities in France.

This article presents the study protocol; it follows the Standard Protocol items: recommendations of the 2013 Interventional Trial (SPIRIT) guidelines [16].

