## Methods/design

### Aim of the study

The main objective of the current study is to evaluate the impact of the *Preventure* program on the prevalence of binge-drinking episodes (i.e, defined as more than 5 standard units of alcohol on a single occasion) among adolescents aged between 14 to 17 and at risk of developing problematic alcohol use, in comparison with usual follow-up care. The secondary objectives are to assess the impact at different times of follow up (3, 6 and 12 months) on 1/ the number of days with alcohol consumption 2/ associated substance uses: tobacco/cannabis, 3/ anxiety and depression, 4/ alcohol-related harm, 5/ quality of life at each stage, 6/ the acceptability of the intervention among French adolescents.

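### Acceptability of the Preventure programme is measured only by study participation and retention, an indirect proxy that says nothing about uptake of the two sessions

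*Protocol article*

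**What the plan says.** Three places in the protocol article concern this point.

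- **Question.** In the Background, "it is also hypothesized that the Preventure program will be considered as an acceptable intervention among French adolescents". The Aim of the study section lists as its sixth secondary objective "the acceptability of the intervention among French adolescents". In both, the thing to be accepted is the programme.
- **Measure.** The Judgment criteria section gives one criterion: "Assessment of the acceptability by adolescents: participation and retention rates in the study". It names no session attendance, no programme completion and no rating of the programme by the adolescents.
- **Programme and follow-up.** The Intervention section says that the "program consists of two 90-min sessions", given to small groups by a trained facilitator. Under Randomisation, "The control group will receive the usual routine follow-up" together with the assessments, while "The intervention group will receive the usual follow-up, assessments plus the Preventure program tailored to one personality type". Follow-up takes place at 1, 3, 6 and 12 months, and "Assessments will be offered to adolescents either by phone or during an interview lasting approximately 1 h".

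**The concern.** The objective is about the intervention and the criterion is about the study. These come apart in both directions. An adolescent who attends neither session but answers every follow-up call is fully retained. One who attends both sessions and then tires of the hour-long assessments counts as lost. Nothing in the article makes attendance a condition of follow-up.

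If the criterion is followed as worded, good retention could be reported as an acceptable programme when few adolescents attended it, and poor retention could reflect assessment burden alone. The Background and Discussion envisage wider roll-out if the trial succeeds. Whether adolescents reached through care networks take up the sessions is a natural question for that decision, and the stated criterion does not address it.

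**Working it through.** The article gives no figure for acceptability, so there is none to reproduce. The check sets the measure against the objective, with a little arithmetic on the planned numbers.

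**Sample size, for context only.** Inputs from the Sample size section: 50% against 35%, alpha 0.05 (taken as two-sided), power 80%. With the mean proportion 0.425:

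n = [1.960 × √(2 × 0.425 × 0.575) + 0.842 × √(0.50 × 0.50 + 0.35 × 0.65)]² / 0.15² = (1.370 + 0.582)² / 0.0225 ≈ 169.3, rounded up to 170 per group.

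This agrees with the article and is not in question.

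**1. Participation.** The Consent section describes written consent, then the SURPS, then randomisation of those with a risk-related trait. Participation is therefore fixed before anyone knows their arm. It shows willingness to join a randomised study and cannot be compared between arms. On planned numbers, 170 of 700 included adolescents (24.3%) are later allocated to Preventure; 530 of 700 (75.7%) are not.

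**2. Retention.** Both arms undergo the assessments and only one receives the programme. If a single pooled rate were reported, 170 of the 340 randomised (50%) would contribute without being offered Preventure. Assumed retention rates, not from the article, show what pooling would hide:

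| Control | Preventure | Pooled |
|---|---|---|
| 90% | 70% | 80% |
| 80% | 80% | 80% |
| 70% | 90% | 80% |

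Reporting by arm separates these three cases.

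**3. What by-arm retention still leaves out.** Cross-classify the 170 Preventure adolescents by retained (yes/no) and attended both sessions (yes/no). Retention fixes one margin only. With an assumed 80% retained, 0.80 × 170 = 136 adolescents, the number attending both sessions can still be anything from 0 to 170. The same holds for any retention rate.

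**4. Precision of a direct measure.** For a proportion p in 170 adolescents, the 95% half-width is 1.96 × √(p(1 − p)/170).

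- p = 0.50: 1.96 × √(0.25/170) = 0.075, or ±7.5 points.
- p = 0.80: 1.96 × √(0.16/170) = 0.060, or ±6.0 points.

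The values of p are assumptions; p = 0.50 gives the widest interval.

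**The case against.** The strongest reply has four parts.

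- **Retention may be compared by arm.** The Statistical analysis section has binary secondary criteria analysed like the main one, by logistic regression between the two groups with adjustment for the stratification factors. Retained or not is a binary criterion, so the plan can be read as giving a by-arm comparison. This stands. A reader might infer that the criterion cannot inform acceptability at all, or that half of those counted are never offered the programme. The first goes too far, because a difference in retention between arms would carry some indirect information. The second holds only for a pooled rate, which the article does not specify.
- **The terms are not defined.** Participation might be meant to include taking part in the sessions, and a condensed article may leave such definitions to the full protocol. This stands in part. However, the article does not leave the measure open: it names one and attaches it to the study. If session attendance was meant, the wording needs correcting anyway.
- **Study participation is relevant to what is new here.** A reader might take online delivery as the novelty under test. The Abstract, the Background and the Strengths and limitations section place it in recruiting through care networks, and the Intervention section mentions online delivery as an adaptation that widens access. Participation does speak to the feasibility of that recruitment, so it should be kept, but under that name.
- **Attendance is also a proxy.** It can reflect the scheduling of groups of about four to six as well as acceptance, and it does not record what adolescents think of the programme. This stands. Attendance is nevertheless closer to the objective than completing an assessment by phone.

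**Conclusion.** The mismatch holds in limited form. The objective concerns acceptability of the intervention. The sole stated criterion combines a rate settled before randomisation with a rate of completing assessments that both arms share. Compared by arm, retention is an indirect and incomplete proxy, and no part of the article ties acceptability to the two sessions.

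Severity is low. One secondary objective is affected; the primary outcome, its analysis and the sample size are not. No size of error can be derived from the article, because it gives no expected attendance or retention. The conclusion rests on reading participation and retention at study level, as the criterion words them, and on follow-up not being conditional on attendance, since the article states no such condition.

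**What to change.** In the Judgment criteria section:

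- Add as the main acceptability measure the proportion of adolescents randomised to Preventure who attend both sessions, with the proportions attending one and none, taken from the facilitator's attendance record.
- Report study participation overall and retention by arm as separate feasibility and attrition measures.

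The cost is a change to one criterion and a small recording task for the facilitator who already leads the sessions. No extra visit or participant is needed. Reasons for non-attendance would help to separate scheduling problems from lack of interest, but collecting them means contacting non-attenders, so they should be optional. The report should say that attendance is itself a behavioural proxy.
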